##### Secondary outcomes

Patient and physician satisfaction measured on a 5-point Likert-scale with the SDM will be analyzed regarding intervention effects. Furthermore, we will collect the following secondary outcomes 12 month after SDM: patients satisfaction with (1) their chosen therapy measured by the global treatment outcome (GTO) [44] and (2) treatment decision measured by the Decision Regret Scale (DRS) [49] to determine if there is exploratory evidence of differences between intervention and control. We will further investigate the fulfilment of the individual expectation between the groups measured on a 5-point Likert-scale, 12 months after SDM. Details on secondary outcome parameters, measurement instruments and time frames are listed in Table 1.

##### Participant timeline

The participant timeline contains the enrollment, two digital assessments (t_0_, t_2_) and the follow-up (t_3_) 12 months after consultation (Fig. 2). The data collected at the various time points are shown in Table 1.

##### Enrollment and pre-Visit assessment(t0)

After screening the patients for inclusion and exclusion criteria within each study site, eligible patients will be informed about the study and asked for participation. Patients willing to participate will sign informed consent and will fill in a digital questionnaire (Table 1) prior to the patient-physician consultation.

##### Intervention (t1)

The study physician will perform clinical examination as usual. Depending on whether the study center is already in the intervention phase, (1) SDM will be performed as usual in routine care or (2) the SDM process will be guided using the EKIT tool.
In the control phase, the study physician will not have access to the additional previously collected patient data. He/she will perform SDM as usual. Information about the chosen therapy will be given as usual.In the intervention phase, the SDM process is guided by the EKIT tool. If TKR is indicated, the patient will receive standardized information about the advantages and disadvantages of the TKR surgery based on IQWIG health information.

##### Post-Visit assessment (t2)

During the control phase and the intervention phase, both the physician and the patient will fill in a digital questionnaire separately. The physician will be asked about her/his satisfaction with the SDM process and will justify the therapy decision on a standardized questionnaire. The patient will be asked about her/his satisfaction with the SDM process and will answer five standard questions about TKR.

##### Follow-Up (t3)

The follow-up will take place 12 months after SDM. Study staff will contact all patients by mail to fill in a questionnaire including current global health status, disease-specific complaints, degree of fulfillment of preoperative expectations, patient satisfaction with the treatment outcome and satisfaction with decision-making and global treatment outcome.

#### Statistical power

The power calculation was based on the primary study outcome (decision quality). A rather conservative scenario to estimate the expected power of the confirmatory analysis was chosen. The calculation was performed for a stepped wedge cluster randomized trials design with a recruitment period of 16 months. Based on a previous study on the effectiveness of a decision aid for patients with osteoarthritis [50], the baseline probability of ‘good decision quality’ measured by DQI-Knee Osteoarthritis [48] was assumed to be 44.5%. Furthermore, we assumed a 10 % increase in decision quality by the implementation of the EKIT tool as decision aid.

We expected 10 participating study sites with an average number of 108 enrolled patients per site over the entire time period (N total = 1,080), accounting for an estimated dropout rate of 11%. The intervention (EKIT tool) was assumed to be implemented sequentially as described in Fig. 1. The modeling of possible correlations within the clusters was performed as part of the data generation process using a logistic multilevel model with a standard deviation of the random intercept of 0.01. Based on these assumptions and a significance level of 5%, the assumed intervention effect on decision quality can be estimated using robust Poisson regression with a power of 89%. The power calculation was performed with the statistical software R [51].

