**Methods:**

The Value-based TKR study is a prospective pragmatic multi-center, stepped wedge, cluster randomized controlled trial (SW-RCT). The EKIT tool provides (1) a systematic presentation of individual patient and disease-specific information (symptoms, expectations), (2) the fulfillment of the indication criteria and (3) health information about safety and effectiveness of TKR. All study sites will follow routine care as control clusters until the start of the intervention. In total, there will be 10 clusters (study sites) and 6 sequential steps over 16 month, with clusters receiving the intervention with a minimum 2 months of standard routine care. The primary outcome is patients’ decision quality measured with the Decision Quality Instrument (DQI)-Knee Osteoarthritis questionnaire. Furthermore, we will collect information on global patient satisfaction, patient reported outcome measures and the fulfilment of the individual expectations 12 months after SDM. The power calculation yielded an estimated power of 89% using robust Poisson regression under the following assumptions: 10 study sites with a total of N=1,080 patients (including a dropout rate of 11%), a 10% increase in decision quality due to the use of the EKIT tool, and a significance level of 5%.

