### Participants, interventions, and outcomes

#### Study setting

The study will take place in ten surgical centers (study sites) in Germany. During routine care, patients are referred to a surgical center by their outpatient primary care physician or orthopedic specialist for a TKR. Study sites will be chosen from different level of care and infrastructural regions in Germany.

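### The stated 89% power is called conservative, but it assumes virtually no between-site variation and is reproduced only for a 10-point absolute effect with no calendar-time term

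*Protocol article*

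**What the plan says.** The Statistical power section opens with "A rather conservative scenario to estimate the expected power of the confirmatory analysis was chosen". It takes a control probability of good decision quality of 44.5% from an earlier decision-aid study and continues "we assumed a 10 % increase in decision quality by the implementation of the EKIT tool", without saying whether the 10% is absolute or relative. It expects 10 sites with 108 patients each (1,080 in total, accounting for 11% dropout). Data were generated "using a logistic multilevel model with a standard deviation of the random intercept of 0.01". The abstract repeats the result: "The power calculation yielded an estimated power of 89% using robust Poisson regression".

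Four other places bear on this:
- Study setting: "Study sites will be chosen from different level of care and infrastructural regions in Germany".
- Study design: each site has at least 2 months of routine care and at least 4 months of intervention within 16 months. The abstract gives 6 steps.
- Confirmatory analysis: robust Poisson regression for clustered data, chosen because it estimates the relative increase directly. No time term is named.
- Methodological considerations: the design carries a higher risk of bias from time effects than a parallel cluster trial. These are expected to be minimal because nothing is known about secular effects on the outcomes.

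**The concern.** Three inputs decide the power of a stepped wedge: how much sites differ, whether calendar time is in the model, and the size of the effect. Here the first is set at practically zero while the scenario is described as conservative. The second is not mentioned. The third is worded so that it can be read two ways with very different power.

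Time matters because the share of patients under the intervention rises with calendar month by construction. An analysis without time credits any drift in decision quality to the tool. An analysis with time loses much of the before-after information. The 89% therefore appears to describe an analysis that is open to confounding by time.

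At stake is how a null result would be read. With 89% stated power it would look like good evidence against a 10-point effect. With power near one half it would not.

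**Working it through.** **Inputs from the article.** Control 44.5%; effect 10%; 10 sites; N = 1,080, or 1,080 × 0.89 = 961 after dropout; random-intercept SD 0.01; alpha 0.05 (taken as two-sided).

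**Assumed.** Figure 1 is not shown. Six equally spaced steps with at least 2 months of control and 4 of intervention put the crossovers at months 2, 4, 6, 8, 10 and 12. Four splits of 10 sites over 6 steps were tried: 2,2,2,2,1,1; 1,1,2,2,2,2; 1,2,2,2,2,1; 2,2,1,1,2,2. The article gives no ICC beyond the SD of 0.01, so 0.01–0.05 is an assumption.

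**Step 1: what SD 0.01 means.** Latent ICC = 0.01² / (0.01² + π²/3) = 0.00003. With logit(0.445) ± 1.96 × 0.01, 95% of sites have true control rates between 44.0% and 45.0%. For scale, an ICC of about 0.01 (SD 0.18) gives 36% to 53%.

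**Step 2: reproduce 89%.** Hussey-Hughes generalised least squares, with residual variance 0.25, gives the standard error (SE) of the absolute effect; power = Φ(0.10/SE − 1.96). For split 2,2,2,2,1,1, N = 1,080, SD 0.01 and no time term: SE = 0.0312, and Φ(3.205 − 1.96) = 0.893. A cluster-robust Poisson simulation of 1,500 runs gave 89.4%. With 961 analysed, the four splits give 86–87%. So 89% fits 1,080 analysed patients better than 961.

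**Step 3: add two-month period effects.** Same split, N and SD: SE = 0.0456, and Φ(2.193 − 1.96) = 0.59. With ICC 0.05: SE = 0.0544, and Φ(1.838 − 1.96) = 0.45. The loss is large partly because months 0–2 and 12–16 (6/16 = 37.5% of the time) contain no within-period comparison.

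Ranges over the four splits and both sample sizes, for 44.5% vs 54.5%:

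| Model | SE (points) | Power, normal | Power, t on 8 df |
|---|---|---|---|
| No time, SD 0.01 | 3.0–3.3 | 86–91% | 75–82% |
| No time, ICC 0.01–0.05 | 3.2–3.6 | 79–88% | 68–79% |
| Period effects, SD 0.01 | 4.2–5.0 | 52–66% | 43–55% |
| Period effects, ICC 0.01–0.05 | 4.7–5.8 | 40–56% | 33–46% |

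The cluster-robust Poisson simulation with period effects (split 2,2,2,2,1,1) gave 64–68% at SD 0.01 (normal test; 52–55% with t on 9 df). At ICC 0.01–0.05 it gave 37–62% (27–47% with t).

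**Step 4: relative reading.** 44.5% × 1.10 = 48.95%, a difference of 4.45 points. In the no-time case of step 2, Φ(0.0445/0.0312 − 1.96) = Φ(−0.53) = 0.30. Across the Hussey-Hughes and simulated cases without time adjustment, power is about 25–38%.

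**Step 5: detectable difference at 80% power, with period effects.** Normal test: (1.96 + 0.84) × SE = 2.80 × (4.2 to 5.8) = about 12–16 points. With t on 8 df the multiplier is 2.31 + 0.89 = 3.20, giving about 13–19 points.

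**The case against.** Several arguments on the other side carry weight.

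- **The figure reproduces.** There is no arithmetic slip: given its inputs and no time term, 89% is right. That stands. The problem lies in the inputs and in how they are described.
- **Between-site variation is the smaller issue.** Without a time term, an ICC of 0.01–0.05 still leaves 79–88% by Hussey-Hughes. A reader might infer from the tiny SD that clustering alone destroys the power; the calculation does not support that.
- **Leaving out time is an inference.** The article says the calculation was done for a stepped wedge rolled out as in Figure 1, and it may have handled time in a way not reported. But no time-adjusted case tried exceeds about 68%.
- **Period terms are commonly left to the analysis plan.** True, and their absence from the article is not itself the point. The power figure and its inputs are printed here, and a later plan that adds period terms would make the 89% wrong for the trial's own analysis.
- **Time effects are argued to be minimal.** The reason given is lack of knowledge about them, which is not evidence that they are absent.
- **The absolute effect can be worked out.** Since only 44.5% vs 54.5% gives 89%, 10 points was presumably meant. A reader might infer that the trial was powered for a relative 10%; the reproduced figure argues against that. What remains is ambiguous wording beside an analysis reported on the relative scale.

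**Conclusion.** The concern holds. An SD of 0.01 is effectively no clustering, so the scenario is favourable rather than conservative. The 89% applies to a 10-point absolute effect analysed without calendar time, and fits about 1,080 analysed patients better than 961.

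With period adjustment and the article's own SD, power is about 52–68% by a normal test and about 43–55% by a small-sample t test. With an assumed ICC of 0.01–0.05 it is about 40–56% (37–62% by cluster-robust Poisson) and roughly 30–45% with a t test. The normal-test Poisson figures may be flattering, because sandwich errors were uncorrected with only 10 sites.

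It would be too strong to say the design simply delivers 35–55%. Figures that low come from combining period effects with an ICC the article does not give, or from a small-sample test it does not name. The result also rests on inferred step timing and site splits, although every split tried led to the same conclusion.

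**What to change.** 1. Include period effects in the primary robust Poisson model.
2. Re-run the power simulation with those effects, a stated ICC range (for example 0.01–0.05, labelled as an assumption) and the small-sample test that will be used with 10 sites.
3. Replace 89% in the abstract and the Statistical power section with the resulting range, and delete the description of the scenario as conservative.
4. Write the effect as 10 percentage points (44.5% to 54.5%, risk ratio 1.22).
5. State whether 1,080 is the number enrolled before, or analysed after, the 11% dropout.
6. Report the difference detectable with 80% power using the same test: about 12–16 points with a normal test, more with a t test.

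The cost is re-running existing simulation code and restating a few figures. No extra patients are needed. The downside is a visibly less favourable power statement.

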#### Recruitment

Each study site was checked for (1) having the necessary number of eligible patients and (2) necessary infrastructure to perform the study. Each study site will be given target numbers for patients to be enrolled in the study per study stage (control, intervention phase). Study sites will competitively recruit up to three consecutive patients per week (the first eligible patients). Achievement of the target numbers will be checked on a monthly basis by the study coordinator. In the case that overall recruitment is 20% lower than planned, the rollout of the interventions will be delayed for all study sites.

### Assignment of interventions

#### Allocation

To minimize the potential bias associated with the fact that the study PI (who already knows the intervention) is also part of a study site, the PI will not enroll patients into the control group, only other study physicians at his site. Randomization of the ten study sites into six sequential steps will be based on computer generated random numbers by the study statistician. The study management will not have the opportunity to influence the randomization process. Consequently, each cluster will initialize the intervention according to the randomly allocated staggered implementation schedule. Study sites gave their consent for the timing of the start of the intervention to be determined by randomization. The study team is responsible for coordinating the timing of study initiation based on the generated allocation sequence.

#### Blinding

Patients, physicians and study staff as well as the study statistician cannot be blinded to the assigned study arm. However, the patients will not receive any further explanation as to which study arm they were allocated to.

### Data collection, management, and analysis

#### Data collection methods and data management

Overall, the majority of data will be collected electronically, with the exception of the follow-up survey. Figure 2 summarizes the data collection process in this study. A web application platform for collection of the data was developed for this study. This web application includes the questionnaires in both phases and additionally the EKIT tool in the intervention phase. Each questionnaire is checked by the web application, ensuring valid answers for all required questions. All data protection issues are detailed in a separate data protection concept.

The follow-up questionnaire (t_3_) will be sent by mail 12 months after t_1_. After four weeks without a response, study staff will send a reminder for the follow-up survey (t_3_). Patients will receive no kinds of incentives or compensation for participation in this study.

#### Statistical methods

All analyses will be evaluated by intention-to-treat principles in terms of assignment to treatment and use a level of significance of 0.05. Study sites, which stop participation after the trial start date or will not implement intervention, will be included in the analysis. There are no interim-analyses planned for this study. We will use the statistical software R [51] for all analyses.

##### Confirmatory analysis

The confirmatory analysis of the primary outcome (decision quality, DQI-Knee Osteoarthritis) [48] is performed as complete case-analysis by estimating the effect of EKIT tool implementation on decision quality using robust Poisson regression for clustered data [52]. The use of this method allows direct estimation of the relative increase in the probability of good decision quality while adequately accounting for the data structure. Furthermore, a regression-based approach allows adjustment for other relevant covariates in the context of sensitivity analyses. Interim analyses were not planned in this study.

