### Study design

The Value-based TKR study is a prospective pragmatic multi-center, stepped wedge, cluster randomized controlled trial (SW-RCT). Each cluster will be randomly assigned to interventions on a staged schedule. In total, there will be 10 clusters (study sites) which will change from control (routine care) to the intervention (EKIT tool) in a predefined randomly allocated sequence. Each cluster will have a minimum 2 months of routine care before changing to the intervention (Fig. 1). At the end of the study, all clusters will be assigned to the intervention with a minimum of 4 months. The total duration of study will be 16 months.

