### Methodological considerations

Compared to conventional parallel cluster randomized controlled trial (cRCT), the choice of the stepped wedges design has a higher risk of bias due to time effects from the staggered nature of the roll-out [54] e.g. if there are secular trends associated with the study outcome [55]. Furthermore, the risk for within-cluster contamination bias is higher than in conventional parallel cRCT [54]. However, we expect these effects to be minimal in this study because there is no knowledge about secular effects on the outcomes (e.g. decision quality and satisfaction) and, if the control phase is successfully implemented, the transition time and expense is minimal.

The power calculation was based on Monte Carlo simulation since analytical solutions for stepped wedged designs drawing on nonlinear statistical models have not yet been established [56]. The systematic review of Eichner, Groenwold [57] shows concerns about reaching the sample size with the stepped wedge design. However, we assume that the advantages outweigh these considerations. To counteract the threat of not reaching a sufficiently large sample size, we made careful arrangements with the study sites before the start of the study.

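### The confirmatory stepped-wedge model states no calendar-time term, so about 0.4 of any linear secular trend would enter the EKIT estimate

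*Protocol article*

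**What the plan says.** In the protocol article, the Confirmatory analysis section defines the primary analysis as a complete-case analysis "estimating the effect of EKIT tool implementation on decision quality using robust Poisson regression for clustered data". EKIT is the only effect it names. On adjustment it says that "a regression-based approach allows adjustment for other relevant covariates in the context of sensitivity analyses". The Sensitivity analysis section then lists multiple imputation and subgroup comparisons, and no time-adjusted analysis.

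The Methodological considerations section of the Discussion recognises that a stepped wedge carries more risk of bias from time effects than a parallel cluster trial. It continues: "we expect these effects to be minimal in this study because there is no knowledge about secular effects on the outcomes". The Statistical power section gives 89% and lists no time effect among its inputs.

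**The concern.** Under Study design, every site begins in routine care and every site finishes on EKIT. Control patients therefore come mostly from early months and EKIT patients mostly from late months. Randomising the order of crossover does not remove this imbalance from a pooled comparison of EKIT with control patients. The usual remedy is to adjust for calendar period.

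The reason given for expecting no problem is that nothing is known about secular effects. Lack of knowledge is a reason to adjust; it is not evidence that no trend exists. Without adjustment, a rising trend in decision quality inflates the EKIT effect and can produce a false positive, and a falling trend can hide a real benefit. This is the trial's only confirmatory test.

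**Working it through.** **Inputs from the protocol article**
- Allocation: "Randomization of the ten study sites into six sequential steps will be based on computer generated random numbers".
- Study design: "Each cluster will have a minimum 2 months of routine care before changing to the intervention"; at the end, "all clusters will be assigned to the intervention with a minimum of 4 months".
- Statistical power: a "stepped wedge cluster randomized trials design with a recruitment period of 16 months"; baseline probability "was assumed to be 44.5"%; a 10% increase; 1,080 enrolled; 11% dropout; random-intercept SD 0.01; 5% level.

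**Assumptions**
- Crossovers at months 2, 4, ..., 12. These fit the stated minima (2 + 5×2 = 12; 16 − 12 = 4), but Fig. 1 is not shown.
- Even accrual over sites and months, and a two-sided test.
- Several ways of splitting ten sites over six steps, written for example as 2-2-2-2-1-1.

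**1. The stated 89%.** Evaluable N = 1,080 × 0.89 = 961. For a risk difference of 0.10:
- SE = √(v / (N·Vx)), where v = (0.445×0.555 + 0.545×0.455)/2 = 0.2475 and Vx is the variance of the EKIT indicator.
- For 2-2-1-1-2-2, 56.25% of patients are on EKIT, so Vx = 0.5625 × 0.4375 = 0.2461.
- SE = √(0.2475/(961×0.2461)) = 0.0324, and power = Φ(0.10/0.0324 − 1.96) ≈ 0.87.

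Simulating robust Poisson regression with EKIT as the only term and a cluster-robust z test gave 0.87–0.90 at N = 961 and 0.89–0.92 at N = 1,080, over four allocations. A separate simulation gave about 0.84. The 89% is thus roughly reproduced without time terms, reading the 10% as percentage points. A relative 10% (44.5% to 48.95%) gives only 28–34%.

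**2. The same calculation with period effects.** Vx becomes the variance of EKIT left within periods, 0.1312 to 0.1062 depending on allocation.
- Best case: SE = √(0.2475/(961×0.1312)) = 0.0443, power 0.62.
- Worst case: SE = √(0.2475/(961×0.1062)) = 0.0492, power 0.53.
- Variance inflation: 0.2461/0.1312 = 1.88 to 0.2461/0.1062 = 2.32.

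Simulated power at N = 961 was 52–62% with individual-level robust SE, 62–69% with cluster-robust z and 48–55% with a small-sample correction. No time-adjusted version exceeded 75%, even at N = 1,080.

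**3. Time gap between phases.** A site crossing at month s contributes s control months centred at s/2 and 16 − s EKIT months centred at (16 + s)/2. Over sites:
- control mean = Σs² / (2Σs)
- EKIT mean = Σ(256 − s²) / (2Σ(16 − s))

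| Sites per step | Control mean month | EKIT mean month | Gap (months) | Gap/16 |
|---|---|---|---|---|
| equal | 364/84 = 4.33 | 1172/108 = 10.85 | 6.52 | 0.41 |
| 2-2-2-2-1-1 | 484/124 = 3.90 | 2076/196 = 10.59 | 6.69 | 0.42 |
| 1-2-2-2-2-1 | 580/140 = 4.14 | 1980/180 = 11.00 | 6.86 | 0.43 |

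The allocation 2-2-1-1-2-2 gives a slightly smaller gap: 628/140 = 4.49 against 1932/180 = 10.73, or 6.2 months (0.39). About 0.4 of a linear 16-month trend therefore enters an unadjusted difference.

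**4. Effect on the test when EKIT does nothing.** The table uses 2-2-2-2-1-1 and about 960 patients. Drift sizes are assumptions, and ranges cover more than one set of simulations.

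| Assumed rise | Spurious RR | Rejection, individual-level robust SE | Rejection, cluster-robust z |
|---|---|---|---|
| none | 1.00 | about 5% | about 10% |
| 2.5 points | 1.03 | 6–7% | 11–12% |
| 5 points | 1.05 | 9–10% | 13–16% |
| 10 points | 1.10 | 25–29% | 30–36% |

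Hand check of the last row, with the rise running from the first to the last period midpoint (14 months):
- control 0.445 + 0.10×(3.90 − 1)/14 = 0.466
- EKIT 0.445 + 0.10×(10.59 − 1)/14 = 0.514
- RR = 1.10. Spreading the same rise over all 16 months gives 0.469 and 0.511, RR 1.09.

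With period effects the RR returned to 1.00 at every drift. Rejection was about 5% with individual-level robust SE, 6–7% with the small-sample correction and 12–13% with uncorrected cluster-robust z.

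**The case against.** The strongest reply is that the article never says time is excluded. It is a condensed text, full model terms are commonly left to an analysis plan, and calendar period is a design factor that need not be among the covariates sent to sensitivity analyses. It is fair that the omission is inferred. The point does not rest on silence, however: the Discussion takes a position on time effects and gives an invalid reason for it. If an unseen plan does add period terms, the published 89% no longer describes the confirmatory test.

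Several stronger readings should be resisted:
- A reader might infer that the power figure proves no time term was planned. It only suggests this: a power model can be simpler than the analysis model, and the match depends on an assumed layout.
- A reader might infer that the whole of a trend is counted as EKIT effect. For a linear trend the share is about 0.4.
- A reader might blame drift for all of the 30–36% rejection with cluster-robust z. About 10% occurs with no drift, because there are only ten sites.
- Changing surgical waiting times might seem an obvious source of drift in the treatment received. The article documents no such mechanism.

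The article's assurance that the method accounts for the data structure is no defence. Cluster-robust variance changes the standard error; it does not remove bias from time.

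**Conclusion.** The concern holds as a defect in the stated confirmatory analysis and in the reason given for it. Its size depends on a drift that nobody knows. At 2.5 points the harm is small. At 10 points, as large as the planned effect, the bias is 4 to 5 points and type I error is five to six times nominal even with individual-level robust SE. The documents do not show that a trend exists, so they do not support saying that the result will be wrong. They support saying that, as described, a positive result could not be separated from drift.

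The figures rest on two-monthly crossovers, even accrual, the assumed allocations of sites to steps, and the article's near-zero between-site variation. A larger between-site SD was not examined.

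**What to change.** In the Confirmatory analysis section, state that the robust Poisson model contains fixed effects for calendar period alongside the EKIT indicator, and that the cluster-robust variance carries a small-sample correction suited to ten sites. Keep the model without time as a sensitivity analysis. In Methodological considerations, remove the statement that time effects are expected to be minimal.

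The text change is short, but the cost in precision is real. At about 960 evaluable patients, power is roughly 48–69% depending on the variance estimator, and 48–55% with the small-sample correction. Part of that fall comes from the correction itself, which gives 76–78% without time terms. The 89% must be restated. By the large-sample formula in step 2, regaining it would take about 1,920 to 2,370 evaluable patients, or 2,150 to 2,660 enrolled at 11% dropout. If that is out of reach, the reduced power should be reported openly.
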